**Methods:**

The sample size for this study is set at 36 participants with slump posture and 36 participants with normal posture. In the first step, to find out the differences between normal and poor posture, they will be asked to perform the typewriting task for 60 min. During the first and last 3 min of typing, mental fatigue as the primary outcome using EEG signals and further measures including kinematic behavior of neck, visual analog fatigue scale, and musculoskeletal discomfort will be assessed. Post-experiment task performance will be calculated based on typing speed and typing errors. In the next step, to compare the effect of tDCS and stretching exercises on the outcome measures, the slump posture group will receive these interventions in two separate sessions before the typing task.

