Exercise and physical activity have been considered as interventions for improving mental fatigue. These interventions increase the performance of the prefrontal cortex, which includes attention, memory, problem-solving, and decision-making [17]. For example, performing targeted stretching micro-breaks in surgeons without increasing the surgery time, improved their performance and concentration [18]. Furthermore, a short-term supervised exercise program including stretching exercises and joint mobility during a work shift has been shown to be more efficient than rest for reducing mental fatigue [19].tDCS is a type of non-invasive electrical stimulation that can change neural excitability in the cortex [20, 21]. tDCS can improve cognitive function in both healthy individuals and neurological patients [22, 23]. According to studies, anodal stimulation enhances learning, memory, and attention [24]. The effect of tDCS has been compared with caffeine as the most common habit to reduce fatigue. Interestingly, tDCS has a greater effect on attention and this effect also lasts longer (6 h) than caffeine (2 h) [25].

A limited number of studies have investigated the non-biomechanical part of poor posture. Most of these articles have used functional tests (such as rate of speaking) to investigate the impact of poor posture, and only one article has examined the correlation between forward head posture and brain signals as measured by a neuro-feedback system [6]; At present, there is an absence of studies utilizing QEEG to track mental fatigue in slump sitting, and in addition, the potential role of slump posture on work productivity needs to be investigated. Given the negative mental state consequences associated with poor posture and the high prevalence of slump sitting, there is a critical need to investigate changes in cortical activity and task productivity in this posture. Previous studies indicate that tDCS and stretching exercises can reduce the adverse effect of mental fatigue, however; no study has compared the effect of transcortical stimulation and stretching exercises in improving mental fatigue with neurophysiological markers of electroencephalography.

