#### Task

Previous research showed that working with a computer for a period of 45 to 60 min had reduced the performance to its minimum level [26]. So, in this study, 60 min are considered for typing, and spell-check of the word program will be turned off for all conditions. Three different Persian texts from a single book are selected for the study. The same text will be used for individuals with normal and slump posture (i.e., no intervention). But for the intervention sessions, the text will be changed to prevent the learning effect.

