### Eligibility criteria {10}

Subjects will be included, if they meet the following criteria: age between 22 and 40 years, have a BSc degree, fluency in Persian, prior experience with computer typing and lack of 10-finger typing skills, no history of shoulder and spine surgery or fracture, no obvious scoliosis, body mass index (BMI) < 30. Postural angles including the craniovertebral angle (CVA) and the thoracic kyphosis angle (TKA) are considered as follows: CVA ≥ 50 and TKA between 20 and 40 for the normal posture group, CVA < 50 and TKA > 40 for the slump posture group. In addition, cardiac or metabolic diseases, severe head injury, metals in the head, psychological problems, seizures, a history of taking medications that affect the central nervous system, and pregnant women will not be included in the study.

The typewriting background will be controlled by a self-report of daily amount of computer usage and years of computer use. There will be no significant difference between the two groups with respect to computer usage.

Before the tests, subjects are asked to follow these: (1) proper and adequate sleep, (2) avoid using drugs or alcohol in the last prior week, and coffee in the last prior 8 h.

Excluding criteria: those individuals who will not be interested in continuing the study for any reason.

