## Data collection and management

### Plans for assessment and collection of outcomes {18a}

Data collection will be performed by one of the investigators of study who will be trained in how to do assessments. Subjects will be familiarized with the equipment and tests of study during screening. For all participants, data collection will be conducted at a certain time before noon, in face-to-face meetings at the motor control laboratory at the School of Rehabilitation of TUMS.

Participants will receive a SMS text or an email to remind their appointment the day before. Principal investigator of the study will supervise data collection to check the quality, completeness, plausibility, and possible errors of the collected data.

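### The pre-test restriction bars coffee but not caffeine, so tea, cola or an energy drink shortly before a morning mental-fatigue test complies with the protocol

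*Protocol article*

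**What the plan says.** Eligibility criteria {10} lists conditions for the period before testing, introduced by "Before the tests, subjects are asked to follow these". They are adequate sleep and the instruction to "avoid using drugs or alcohol in the last prior week, and coffee in the last prior 8 h". Coffee is the only caffeine source named.

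Background and rationale {6a} speaks of the stimulant itself: "The effect of tDCS has been compared with caffeine as the most common habit to reduce fatigue". It adds that the effect on attention lasts 2 h for caffeine and 6 h for tDCS.

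On timing, section {18a} states that for all participants "data collection will be conducted at a certain time before noon", and the Task section says "60 min are considered for typing". The abstract gives "mental fatigue as the primary outcome using EEG signals", assessed in the first (T1) and last (T2) 3 min of typing. A visual analog fatigue scale is among the secondary measures.

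Section {20c} says that outcome data arising from non-adherence to the protocol will not be used.

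**The concern.** The evident purpose of the coffee condition is to keep a stimulant out of a fatigue test. The protocol names that stimulant as caffeine, yet the rule removes only one source of it. This is a stated rule that misses its own target, not a detail left to another document.

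Two comparisons are exposed, in different ways. The slump and normal groups are formed by postural angles, not by randomisation, so a difference in habitual intake of other caffeine would be mixed with the posture effect on the EEG and fatigue-scale outcomes. The same holds for the secondary comparisons of treated slump participants with the normal group. In the crossover, intake that varies between one person's three sessions enters the contrasts between tDCS, stretching and no intervention.

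**Working it through.** No sample size, error rate or power figure depends on this point, and the plan states no figure to reproduce. The check sets the passages side by side, with one piece of timing arithmetic.

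**1. Does any other word in the rule cover caffeine?** The only candidate is the reference to drugs. Drugs and alcohol carry a one-week window, whereas coffee has its own of 8 h. Had caffeine counted as a drug, coffee would already have been barred for a week and the separate condition would be pointless. So non-coffee caffeine is not restricted.

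**2. Does the 8 h window reach the relevant drinks?** Testing is before 12:00, so the window opens before 12:00 − 8 h = 04:00. Anything drunk at breakfast falls inside it. The window is also four times the cited duration of effect (8 h / 2 h = 4). Its length is not the problem; the substance named is.

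**3. Can permitted caffeine overlap the measurements?** Inputs: a 2 h (120 min) effect from {6a}, a 60-min task, T1 at minutes 0–3 and T2 at minutes 57–60. Let x be the minutes from intake to the start of typing. Counting the 2 h from intake (an assumption), the effect ends 120 − x minutes into the task.

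| x (min) | Effect ends at task minute | T1 | T2 |
|---|---|---|---|
| 60 or less | 60 or later | covered | covered |
| 63 to 117 | 57 down to 3 | covered | not covered |
| 120 or more | 0 or earlier | not covered | not covered |

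(At 60–63 and 117–120 one recording is partly covered.) The time from arrival to typing is not stated. It includes preparation and, in two of the three slump sessions, an intervention of about 10 min. A drink shortly before arrival could fall in the first or second row. In the second row, T1 is recorded under the effect and T2 after it, which would bear on the change over the task as well as on its level.

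**4. Does the non-adherence rule catch it?** Section {20c} removes data from protocol non-adherence. A participant who drank tea has followed the instruction as written, so the rule does not apply.

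**5. What follows in each part?**
- *Slump versus normal:* bias arises if non-coffee caffeine before the session differs between groups. The baseline characteristics given as examples in {20a} include computer use but not caffeine.
- *Crossover:* all six session orders are used equally under {16a}, so intake unrelated to condition does not favour one condition systematically. It adds within-person variability and costs precision.

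**The case against.** The strongest reply is that coffee is loose wording for caffeine, that staff would explain this in practice, and that the link to the primary outcome is unproven. The last part stands: the 2 h figure concerns attention, comes from a cited comparison with tDCS, and is not tied anywhere in the document to relative EEG band power. The overlap in the table is therefore a possibility, not a demonstrated effect. The first part does not dispose of the point, because participants act on the wording given and the protocol uses the two words in different places.

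Three stronger readings are tempting and are not supported.

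- *That the conditions have no consequence, so a participant who breaks them is simply tested.* A reader might infer this from the request form and from "Excluding criteria: those individuals who will not be interested in continuing the study for any reason". But {20c} does attach a consequence to non-adherence, {18a} has the principal investigator supervise data quality, and the text nowhere says that such a person is tested regardless. Arrival checks and rebooking rules are operational detail that an article may leave out. For the same reason, no separate finding about short sleep follows.
- *That a definite share of participants would have a different caffeine state between sessions.* This needs the prevalence of non-coffee caffeine and its correlation across a person's sessions. The document gives neither, and a fixed morning habit would make sessions alike.
- *That uneven intake could systematically mimic a treatment effect in the crossover.* Randomised order argues against this; noise is the main consequence.

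It is also fair to say that section {8} describes the posture comparison as exploratory, and that nothing in the document shows the groups to differ in caffeine habits.

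**Conclusion.** The point holds in a limited form. The restriction names coffee, the protocol's rationale names caffeine, and morning sessions leave room for permitted caffeine whose cited 2 h duration can span part or all of a 60-min task. The non-adherence rule does not reach it.

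The consequence is conditional. There is possible confounding in the non-randomised posture comparison if intake differs by group, and mainly some loss of precision in the crossover. Neither can be sized from the document. The conclusion rests on two assumptions: that the coffee condition was meant to exclude a stimulant effect, and that an effect on attention is relevant to the fatigue outcomes. This is a modest weakness, worth correcting because the correction is nearly free.

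**What to change.** Reword the condition in Eligibility criteria {10} so that it covers any caffeine-containing product (coffee, tea, cola, energy drinks and similar), keeping the 8 h already stated. At each session, in both groups, record the time and type of last caffeine intake. Intake inside the window then becomes identifiable non-adherence to which {20c} can be applied, and the slump and normal groups can be compared on it.

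The cost is a slightly stricter instruction and one extra question per session.

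The Trial status section expected recruitment to finish on 5 February 2023, before the article appeared. If the sessions have already been run, intake cannot be reconstructed reliably. The coffee-only restriction should then be reported as a limitation, chiefly of the posture comparison.

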#### Postural angle measurements

Photogrammetry is a safe, accessible, and inexpensive technique, that provides an accurate postural angle measurement [27]. Postural angles as a baseline criterion will be measured. For this, the spinous processes of the seventh cervical (C7) and twelfth thoracic (T12) vertebrae and tragus will be marked by palpation, and reflexive markers will be attached to these points. The camera will be placed 120 cm away from the participant at a height of 130 cm [27]. The photography will be done from the sagittal plane with a camera (SAMSUNG, A50, South Korea). The photograph will then be imported to AutoCAD software version 24. To assess the posture of the head, we will use CVA, which is obtained by the intersection of a horizontal line passing through the C7 marker and a line joining the tragus to the C7 marker [28]. To measure the angle of thoracic kyphosis, we will draw a straight line between C7 and T12 markers, and then a perpendicular line is drawn on each of the lines. The intersection of the perpendicular lines makes an angle which is considered TKA [27].

### Who will take informed consent? {26a}

At the start of the study, the investigator will evaluate the subjects for inclusion and exclusion criteria, explain the study in detail and answer the questions. Then all participants will be asked to read and sign the consent form which is approved by the Ethics Committee of TUMS with the ID IR.TUMS.FNM.REC.1401.069. This form has information such as the title and goals of the study, the names of researchers, research background, how the interventions will be conducted, and obligations.

### Additional consent provisions for collection and use of participant data and biological specimens {26b}

The study will not involve collecting biological specimens therefore, there is no need for additional consent provisions. All the steps of this research will be done based on the consent form which explains what study participation entails, the research process and the potential benefits and risks of the study.

## Interventions

### Explanation for the choice of comparators {6b}

The normal posture group will participate just once while the slump posture group will carry out the experiment in 3 separate sessions (i.e., no intervention, stretching exercise, and tDCS) with a week interval between sessions. The sequence of sessions will be randomized. The assessor involved in analyses will be blind to groups and conditions.

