## Assignment of interventions: allocation

### Sequence generation {16a}

Randomization sequence will be generated using a web-based randomization service (https://statpages.info/latinsq.html). Given three states for slump posture group (i.e., no intervention, tDCS, and stretching exercise), there will be six different possible orders (ABC, ACB, BAC, BCA, CAB, and CBA). Each order will be performed five times in an equal ratio.

Randomization will be done at TUMS. Access to the randomization schedule will be restricted to an investigator who is not involved in the recruiting process.

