## Statistical methods

### Statistical methods for primary and secondary outcomes {20a}

Data analysis will be performed using SPSS, version 22 (IBM, NY, USA). Baseline characteristics such as age, weight, height, BMI, years of computer use, and daily computer usage will be summarized with standard descriptive statistics. Depended variables will be described with means and standard deviations. The normality of distribution will be checked by Kolmogorov–Smirnov.

Multivariate ANOVA (MANOVA) will be used to compare the variables between correct and slump posture groups.

Statistical analysis of the outcomes of 3 conditions in the slump posture group will be conducted using repeated measures ANOVA and LSD (least significant difference) post hoc test. The significance level of tests will be considered at 0.05. Mean difference and standardized mean difference and their 95% confidence intervals (Cohen’s D) will be calculated as effect sizes.

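### The slump-versus-normal contrasts mix posture with repeat attendance, because normal participants are all on a first session and most slump sessions are not

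*Protocol article*

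**What the plan says.** The section on comparators ({6b}) states that "The normal posture group will participate just once while the slump posture group will carry out the experiment in 3 separate sessions", one week apart, and that "The sequence of sessions will be randomized". Sequence generation {16a} confirms that the untreated session is part of the randomisation: "Given three states for slump posture group (i.e., no intervention, tDCS, and stretching exercise), there will be six different possible orders", and "Each order will be performed five times in an equal ratio". The Task subsection gives the normal group the same text as the slump no-intervention session, so that session is the slump side of the posture comparison.

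Two analyses are stated under Statistical methods {20a}. For the posture comparison, "Multivariate ANOVA (MANOVA) will be used to compare the variables between correct and slump posture groups". For the crossover, "Statistical analysis of the outcomes of 3 conditions in the slump posture group will be conducted using repeated measures ANOVA", followed by LSD tests. Neither mentions session, period or sequence, and section {20b} says there will be no additional analyses.

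The protocol does treat learning as a threat. It changes the text for the intervention sessions (Task), and participants practise before the experiment (Study setting {9}).

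**The concern.** The two sides of the posture comparison differ in more than posture. A normal participant meets the hour of typing and the EEG set-up for the first time. Most slump participants reach their untreated session after doing the task once or twice before, in some cases after stretching or tDCS a week or two earlier. Any effect of having attended before, such as practice, habituation or boredom, is added to the posture difference, and a MANOVA by group cannot separate the two.

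The slump-versus-normal contrast is the main objective. The contrasts of treated slump sessions with normal have the same defect, because each condition is in first position in only 2 of the 6 orders. A spurious posture effect, or a masked real one, could follow.

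**Working it through.** **Inputs from the protocol.** Six orders with five replicates each ({16a}): 6 × 5 = 30 slots, which agrees with the 30 slump participants required in {14}. Part 1 requires 50 participants, or 25 per group; planned enrolment is 36 per group ({14}).

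**Assumption.** The protocol gives no session effect, so a range of 0.1 to 0.5 SD is shown.

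**Step 1: position of the no-intervention session.** Over the six permutations it is first, second and third in 2 orders each. It is not first in 4 of 6 orders: 4 × 5 = 20 of 30 slots. In the normal group the corresponding number is 0.

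**Step 2: bias in Part 1.** With p2 and p3 the session 2 and 3 effects relative to session 1, the slump mean contains (0 + p2 + p3)/3 and the normal mean contains 0. So bias = (p2 + p3)/3.
- Linear effect, p2 = e and p3 = 2e: bias = 3e/3 = e.
- One-off step after session 1, p2 = p3 = e: bias = 2e/3.

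**Step 3: type I error in Part 1.** For a single outcome, use a two-sample t test with equal SDs, two-sided 0.05, no true posture difference, 2n − 2 degrees of freedom and noncentrality bias × √(n/2). The extra spread that session effects add within the slump group is ignored. Example: e = 0.3, linear, n = 36 gives noncentrality 0.3 × √18 = 1.27 and rejection 24%.

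| e (SD) | Linear, n = 25 | Linear, n = 36 | Step, n = 25 | Step, n = 36 |
|---|---|---|---|---|
| 0.1 | 6.4% | 7.0% | 5.6% | 5.9% |
| 0.2 | 10.7% | 13.3% | 7.5% | 8.6% |
| 0.3 | 18.0% | 24.1% | 10.7% | 13.3% |
| 0.5 | 41.0% | 55.3% | 21.1% | 28.6% |

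**Step 4: Part 2.** With balanced orders each condition occurs equally often in each session, so session effects cancel from the condition contrasts; the simulated bias was about 0. They remain in the error term: E(MSE)/s² = 1 + n × Σ(p_j − p̄)² / (2(n − 1)), where s² is the within-subject variance. For a linear effect of e within-subject SD per session, Σ(p_j − p̄)² = 2e². At n = 30 this gives 1.01, 1.04, 1.09 and 1.26 for e = 0.1, 0.2, 0.3 and 0.5. In simulation, with both interventions shifted by an illustrative 0.8 within-subject SD, power without and with a session term was 0.866 and 0.887 at e = 0.3, and 0.810 and 0.888 at e = 0.5. Without the term the test is conservative (type I error 0.025 at e = 0.5).

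**Step 5: cost of adjusting Part 1.** In units of the outcome variance, the unadjusted contrast has variance 2/n. Estimating the session effects within slump participants adds (2/3)(1 − ICC)/n. The SE ratio is therefore √(1 + (1 − ICC)/3): 1.11, 1.08 and 1.05 at assumed intraclass correlations of 0.3, 0.5 and 0.7.

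**The case against.** The best defence is that the protocol already limits the problem. Everyone practises beforehand, prior typing experience is required, sessions are a week apart and the text changes for the intervention sessions. These measures reduce the session effect. They do not equalise one or two full earlier sessions, because new text prevents recall of content but not familiarity with the task and laboratory.

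A second defence is that the primary outcome is EEG, recorded in the first and last 3 minutes of typing. A session effect that is constant within a session cancels in T2−T1 change. This stands as a limit on the concern: bias in the fatigue contrast is possible, not established. The protocol does not say whether change is what the MANOVA compares.

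Three stronger readings are tempting and not supported.
- A reader might take one figure, such as 24%, as the type I error of Part 1. It requires a linear 0.3 SD effect at 36 per group; a 0.1 SD effect gives about 6% to 7%.
- A reader might infer that the crossover analysis is biased as well. With balanced orders it is not, and a period term is a detail an unseen analysis plan may supply. Drop-out could unbalance the orders, but nothing in the protocol allows that to be sized.
- A reader might infer that the abstract contradicts the randomised order, since it presents the posture comparison as a first step and then says "the slump posture group will receive these interventions in two separate sessions before the typing task". Those steps can be the two parts of the study, and the abstract nowhere says that the untreated session comes first.

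**Conclusion.** The point holds for the contrasts with the normal group. That first visits are compared with mostly repeat visits follows from the protocol's own design and needs no assumption. The stated MANOVA does not address it.

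The size is conditional. The bias is one session's effect if the effect is linear, and two thirds of it if it is a one-off step. Over an assumed 0.1 to 0.5 SD and 25 to 36 per group, two-sided type I error runs from about 6% to 55% (linear) or 6% to 29% (step). The direction is unknown for EEG; the risk is clearest for typing speed and errors. For the three slump conditions the consequence is lost precision only, with an error mean square 1% to 26% larger over 0.1 to 0.5 within-subject SD per session.

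**What to change.** For each outcome, fit a linear mixed model with T2−T1 change as the response where both are measured. Include a four-level factor (normal; slump with no intervention, stretching, tDCS), session number (1, 2, 3) as a fixed factor and a random participant effect. Take the contrasts with normal at session 1. The balanced orders in the slump group identify the session effects, and the same model gives the three contrasts among slump conditions with the session variation removed from the error.

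As a check, compare normal participants with slump participants whose first session was no-intervention: 10 of 30, or 12 of 36 if the orders are extended equally. This is free of session and carry-over effects but imprecise: with 10 against 30, the SE is √(1/10 + 1/30) / √(2/30) = 1.41 times that of the full comparison.

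The change is to analysis wording only. It costs about 5% to 11% in the SE of the posture contrast, and it assumes that session effects are additive and that nothing carries over after one week.

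A minor edit: state in the abstract that its two steps are parts of the study and not the order of sessions.
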